## Methods/design

This study is designed as a randomized phase II study. Patients will be randomized between current standard of care treatment (Arm 1) vs. standard of care treatment + SABR (Arm 2) to sites of known disease (Figure 1). Patients will be randomized in a 1:2 ratio to Arm 1 vs. Arm 2, respectively. This study has been approved by the Ontario Cancer Research Ethics Board (#11-030), in compliance with the Helsinki Declaration.

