## Statistical analysis

### Sample size

This study will employ a randomized phase II design, to conduct a preliminary and non-definitive randomized comparison between the control and experimental arms. The study will aim to detect a signal in improved overall survival that would be used to design a phase III study to definitely compare survival outcomes between the two groups. The study will therefore be designed with alpha = 0.20 and beta = 0.20 (as recommended for phase II randomized studies [23]). It is estimated that the median survival of the control group after randomization in this study will be 9 months.

There will be a 1:2 randomization between Arm 1 and Arm 2. In order to detect a 6-month improvement in median survival from 9 months to 15 months with SABR, a total of 93 patients (31 in Arm 1 and 62 in Arm 2) will be needed. Assuming a 5% rate of loss to follow-up, a total of 99 patients will be accrued (33 in Arm 1 and 66 in Arm 2). The study projects accrual over 48 months with 12 months of additional follow-up. Accrual targets are as follows: 20 patients in year 1, and 25-30 patients in years 2, 3, and 4.

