#### Secondary endpoints

Quality of life at 6 months will be measured using FACT-G scores, with differences between groups tested using the Student’s *t*-test. Differences in rates of grade 2 or higher toxicity between groups will be tested using the Fisher’s Exact Test. Differences in progression free survival will be tested using the stratified log-rank test. Differences in the number of cycles of further chemotherapy/systemic therapy will be tested using the Student’s *t*-test.

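### Student's pooled-variance t-test is named for 6-month FACT-G and cycles of systemic therapy under 1:2 allocation, where it holds its error rate only if the arms have equal variance

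*Protocol article*

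**What the plan says.** The Secondary endpoints paragraph of the protocol article's Data analysis section names the same test for two endpoints:

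- FACT-G: "Quality of life at 6 months will be measured using FACT-G scores, with differences between groups tested using the Student’s" *t*-test.
- Systemic therapy: "Differences in the number of cycles of further chemotherapy/systemic therapy will be tested using the Student’s" *t*-test.

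The unequal allocation is deliberate. Methods/design says "Patients will be randomized in a 1:2 ratio to Arm 1 vs. Arm 2, respectively", and Sample size gives the numbers: "a total of 99 patients will be accrued (33 in Arm 1 and 66 in Arm 2").

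The article does not mention unequal variances, a rank test, a count model or a transformation for these endpoints. It gives no SD and no significance level for them, and it does not promise confidence intervals.

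**The concern.** Student's test estimates one common variance from both arms and uses it in the standard error of the mean difference. With equal arms, that standard error equals the correct one whatever the two variances are. With twice as many patients in the SABR arm, the pooled variance is mostly the SABR arm's. If the control arm is the more variable, the standard error is too small and the test rejects too often. If the SABR arm is the more variable, the standard error is too large and the test is conservative.

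Unequal spread is plausible for cycles, because the spread of a count usually rises with its mean. For FACT-G, the imbalance grows if deaths before 6 months fall more heavily on the control arm. Both comparisons are meant to help inform a phase III design, so the p-values, and any intervals reported with them, should not depend on an untested equal-variance assumption.

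**Working it through.** **1. Arm sizes.** These follow from the primary-endpoint calculation, which can be reproduced. Inputs from Sample size: medians of 9 and 15 months, 48 months of accrual plus 12 of follow-up, alpha 0.20, beta 0.20, 1:2 allocation. Assumed: exponential survival, uniform accrual, two-sided alpha.

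- Hazard ratio 9/15 = 0.60, and (ln 0.60)² = 0.261.
- Death probability is 1 − [exp(−12λ) − exp(−60λ)]/(48λ) with λ = ln 2/median. This gives 0.895 (control), 0.769 (SABR) and 0.811 overall.
- n₁ = (1.282 + 0.842)²/0.261 × [1/0.895 + 1/(2 × 0.769)] = 30.5, and 2n₁ = 61.05.
- Rounded up, 31 + 62 = 93, as stated. Then 93/0.95 = 97.9, so 98, and 99 is the next total that splits 1:2 (33 and 66).

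**2. Arm sizes at 6 months.** If only survivors contribute FACT-G, the medians hold and every survivor returns a form: 33 × 2^(−6/9) = 20.8 and 66 × 2^(−6/15) = 50.0, about 21 and 50.

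**3. Standard-error ratio.** Let r = control SD / SABR SD, with the SABR SD set to 1. Then

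(pooled SE / true SE)² = [((32r² + 65)/97) × (1/33 + 1/66)] / [r²/33 + 1/66].

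- r = 2: (193/97 × 0.04545)/0.13636 = 0.0904/0.1364 = 0.663; square root 0.81.
- r = 0.5: (73/97 × 0.04545)/0.02273 = 0.0342/0.0227 = 1.505; square root 1.23.
- With n per arm in both arms, both squared SEs equal (r² + 1)/n, so the ratio is 1 at every r. The distortion comes from the 1:2 split.

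**4. Rejection rates.** Normal data, equal means, 100,000 simulated data sets per setting. The values of r are assumptions, because the documents give no SD. The levels are illustrative: 5% is conventional, and 20% is the design alpha for the primary endpoint.

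| r | SE ratio, 33/66 | Student 5%, 33/66 | Welch 5%, 33/66 | Student 20%, 33/66 | Student 5%, 21/50 |
|---|---|---|---|---|---|
| 0.5 | 1.23 | 1.7% | 5.0% | 11.7% | 1.2% |
| 0.67 | 1.14 | 2.6% | 4.9% | 14.5% | 2.2% |
| 0.8 | 1.08 | 3.5% | 5.0% | 16.7% | 3.3% |
| 1 | 1.00 | 5.0% | 5.1% | 20.1% | 4.9% |
| 1.25 | 0.93 | 6.8% | 5.0% | 23.3% | 7.2% |
| 1.5 | 0.88 | 8.5% | 5.1% | 26.0% | 9.4% |
| 2 | 0.81 | 11.0% | 5.0% | 29.8% | 13.1% |

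**5. Cycles as skewed counts** (negative binomial, assumed, 33/66).

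- Same distribution in both arms (mean 4, dispersion 1): Student rejects 4.8%, Welch 5.3%. Skewness and 1:2 allocation alone do no harm.
- Means 6 (control) and 3 (SABR), dispersion 1: the variances are 6 + 36 = 42 and 3 + 9 = 12, an SD ratio of 1.87. Coverage of the 95% interval is about 89% pooled and about 94% with Welch.
- Means 3 and 6: coverage is 97.7% pooled and 95.2% with Welch.
- Equal means of 4 but SDs of 6.0 and 3.5: Student rejects 10.4%, Welch 7.4%.

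**6. Cost when SDs are equal** (33/66, 5% level). Power is 63.9% (Student) against 63.4% (Welch) at a standardized difference of 0.5, and 79.4% against 78.9% at 0.6.

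**The case against.** The strongest reply is that nothing shows the equal-variance assumption failing here. The documents give no SD. Both arms meet the same entry criteria, and a quality-of-life score has no obvious reason to be nearly twice as variable in one arm. At ratios of 0.8 to 1.25 the error rate moves only to 3.5–6.8% (33/66) or 3.3–7.2% (21/50), and the direction is unknown. This stands: the extreme rows of the table show sensitivity and do not predict what will happen.

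Two stronger readings are tempting. A reader might infer that the test is really one of equal means and equal spread together. It is not aimed at spread. It keeps its level when SABR leaves the distribution unchanged, which is a natural null under randomization. A reader might also infer that the link between mean and spread in cycles inflates false positives. If spread follows the mean, equal means imply equal spread, so that link alone causes no inflation. What it affects is interval coverage when the means differ. Since the article promises only tests, that point concerns an interval reported alongside the named test.

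It can also be said that the label is sometimes used loosely and that an analysis plan not shown here may specify the version. That is possible, but the article names Student's test without qualification, and by name that is the pooled test.

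Finally, Welch is not a full cure for skewed counts, as the 7.4% figure shows. That also stands.

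**Conclusion.** The point holds as a conditional one. For both endpoints the named test keeps its nominal level under 1:2 allocation only if the arms have equal variance. For normal data with equal means at 33/66, the departure at a nominal 5% runs from 1.7% to 11.0% over SD ratios of 0.5 to 2, and is modest at ratios near 1. The 21/50 figures rest further on the design medians, survivors-only analysis and complete forms. For cycles, the practical effect is mainly on interval coverage: about 89% pooled against 94% with Welch in the assumed example of means 6 and 3.

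The documents do not support saying that the error rate in this trial is wrong, or in which direction. The primary endpoint uses a log-rank test and is untouched, the sample size reproduces, and no stated decision or stopping rule depends on either *t*-test. This is a low-priority improvement.

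**What to change.** In the Secondary endpoints paragraph of Data analysis, replace Student's *t*-test with Welch's unequal-variance *t*-test for both 6-month FACT-G and number of cycles, or with a model using robust standard errors. If a confidence interval for the mean difference is reported, take it from the same unequal-variance method.

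The cost is a short text change and a software option, plus about half a percentage point of power if the variances turn out equal. Making the change before outcome data are seen also avoids choosing the test afterwards. For cycles, the team should expect some residual distortion if the counts are strongly skewed and the arms differ in spread.

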### Data safety monitoring committee

The DSMC will meet annually after study initiation and after 50 patients are accrued to review toxicity outcomes. If any grade 3-5 toxicity is reported, the DSMC will review the case notes to determine if such toxicity is related to treatment. If the DSMC deems that toxicity rates are excessive (>25% grade 3 toxicity, or >5% grade 4 or 5 toxicity), then the DSMC can, at its discretion, recommend cessation of the trial, dose adjustment, or exclusion of certain treatment sites that are deemed as high-risk for complications.

The DSMC will conduct one interim analysis once 50 patients are accrued. For this analysis, the DSMC will be blinded to the identity of each treatment arm, but OS data will be presented for each arm. The DSMC will recommend stopping the trial if there is an OS difference that is statistically significant with a threshold of p < 0.001 using the log-rank test. Furthermore, if the median OS among all patients is substantially different than estimated in the sample size calculation, the DSMC can recommend increasing or decreasing the target accrual in order to maintain statistical power.

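### The 50-patient interim claims a blinding that 1:2 allocation defeats, and the committee that sees survival by arm may then recommend a new sample size on an unquantified trigger

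*Protocol article*

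**What the plan says.** All references are to the protocol article.

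- **Allocation.** Under Methods/design: "Patients will be randomized in a 1:2 ratio to Arm 1 vs. Arm 2, respectively". Evaluation and randomization adds one two-level stratification factor (1-3 or 4-5 metastases) and permuted blocks of nine.
- **Interim look.** Under Data safety monitoring committee, there is one analysis once 50 patients are accrued. For it, "the DSMC will be blinded to the identity of each treatment arm, but OS data will be presented for each arm". The committee recommends stopping if the log-rank test gives p < 0.001.
- **Re-sizing.** The same paragraph adds that, if median survival in all patients together is substantially different from what the sample size calculation estimated, "the DSMC can recommend increasing or decreasing the target accrual in order to maintain statistical power".
- **Design estimate.** Under Sample size, the trial is "designed with alpha = 0.20 and beta = 0.20". For controls: "It is estimated that the median survival of the control group after randomization in this study will be 9 months". The target is a "6-month improvement in median survival from 9 months to 15 months with SABR", for which "a total of 93 patients (31 in Arm 1 and 62 in Arm 2) will be needed". This is raised to 99 for loss to follow-up. No all-patient median is given.

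**The concern.** There are two linked problems.

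First, the article states a safeguard that its own design removes. When one arm is planned to be twice the other, coded labels hide nothing once numbers at risk, death counts or Kaplan-Meier step sizes are shown by arm.

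Second, the committee that has just seen the survival comparison also holds discretion over final accrual, in either direction. The trigger has no stated threshold, and its reference value does not appear in the calculation it points to. If the survival difference colours the recommendation, the final log-rank test is run on a sample size that depends on the interim effect, and an unadjusted test then rejects too often. Even if nothing of the kind happens, the trial would be unable to show that it did not.

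**Working it through.** **1. The plan's own sample size.** Inputs from Sample size: medians 9 and 15 months, alpha 0.20, power 0.80, 1:2 allocation, 48 months' accrual plus 12 months' follow-up. Exponential survival and uniform accrual are assumed. Sidedness is not stated.

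- Hazard ratio = 9/15 = 0.60.
- Deaths needed, two-sided (Schoenfeld): (1.2816 + 0.8416)² / [(1/3)(2/3)(ln 0.60)²] = 4.508 / 0.0580 = 77.7, so 78.
- Probability of death by the end: 0.895 control, 0.769 SABR, 0.811 overall. Then 93 × 0.811 = 75.4 deaths, giving power 0.791.
- Log-hazard-ratio formula, with p₀ = 0.825 at the average hazard: N = {[1.2816√(4.5/p₀) + 0.8416√(3/0.895 + 1.5/0.769)] / 0.5108}² = 93.2.

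The stated 93 is reproduced with two-sided alpha. One-sided alpha gives only about 58 to 61. Also 93/0.95 = 98, raised to 99, which fits 1:2 and blocks of nine.

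**2. Can coded arms be told apart at 50 patients?** Each full block holds 3 Arm 1 and 6 Arm 2 patients. Since 50 = 5 × 9 + 5, the incomplete blocks of the two strata hold either 5 patients in total (five full blocks, 15 in Arm 1) or 14 (four full blocks, 12 in Arm 1).

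- Most Arm 1 patients: remainders 2 and 3, all in Arm 1: 15 + 5 = 20. With 14 left over, at most 12 + 6 = 18.
- Fewest: with 5 left over, none in Arm 1: 15. With 14 left over (7 and 7, or 6 and 8), at least 2 must be in Arm 1: 12 + 2 = 14.

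Arm 1 holds 14-20 and Arm 2 holds 30-36. The ranges do not meet, so the larger arm is always SABR.

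**3. What pooled median does the design imply?**

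- Alternative: solve (1/3)exp(-t ln2/9) + (2/3)exp(-t ln2/15) = 0.5, giving t = 12.55, about 12.6 months.
- Null at the control rate: 9 months.

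The benchmark therefore depends on the treatment effect. About 22 deaths are expected at the look under the alternative. An approximate 95% interval is 12.55 × exp(±1.96/√22) = 8.3 to 19.1 months, which contains both values.

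**4. Alpha if the pooled trigger is followed.** The article gives no rule, so one was assumed: N becomes 70 if the pooled median is below 0.75 of the reference, 150 if above 1.333 times it, and otherwise stays at 99. The reference was 9 or 12.7 months (close to the value in step 3). Four null scenarios were simulated, with 20,000 trials each, an unstratified log-rank test and Monte Carlo standard error about 0.003.

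- Fixed N = 99 with the p < 0.001 look: 0.201-0.209 (analytically 0.2002).
- Pooled-median re-sizing: 0.201-0.206.

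There is no material inflation.

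**5. Alpha if the by-arm result drives the choice.** Let z be the interim statistic at d₁ deaths and d the final deaths. Under the null, the conditional chance of final rejection is

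CP(z, d) = 1 - Φ[(1.2816√d - z√d₁)/√(d - d₁)] + Φ[(-1.2816√d - z√d₁)/√(d - d₁)].

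Take the largest CP over the allowed d for each z, set it to 1 where |z| > 3.29, and average over the standard normal distribution of z. The limits on d are assumptions.

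| Final deaths allowed | d₁ = 22 | d₁ = 26 | d₁ = 30 |
|---|---|---|---|
| 78 only | 0.200 | 0.200 | 0.200 |
| 62-94 | 0.215 | 0.218 | 0.222 |
| 62-120 | 0.221 | 0.226 | 0.230 |
| 40-120 | 0.247 | 0.257 | 0.269 |
| d₁-160 | 0.355 | 0.352 | 0.349 |

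About 26 interim deaths are expected under the null with a 9-month median. A cruder by-arm rule (N = 70 if |z| is at least 0.9 × 1.2816, otherwise 150) gave 0.232-0.238 by simulation.

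**The case against.** The strongest reply is that the stated trigger is the median in all patients, with the purpose of preserving power. That is a pooled criterion, and step 4 shows that it leaves alpha where it was. The larger figures in step 5 describe a committee that departs from its trigger and picks the most favourable number of deaths. The limits are assumed, and the trial calls itself preliminary and non-definitive. All of this stands. A reader might infer that the final test has lost its 0.20 error rate, but the documents do not support that.

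Nor is failed masking itself what puts alpha at risk. An unmasked committee is not an error-rate problem, and survival shown by coded arm would reveal the size of the difference even if the labels worked. That also stands. The two issues need separate repairs.

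The committee only recommends, and thresholds or limits may sit in a full protocol or charter that is not shown. Their absence from an article is therefore not the finding. What remains is in the text: a blinding statement that cannot be true in effect, a pointer to an all-patient estimate that the sample size section does not contain, and one body holding both the by-arm results and the re-sizing discretion.

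A reader might also infer that harm is guarded only by the symmetric p < 0.001 rule. The same section provides separate review of grade 3-5 toxicity with its own discretionary thresholds, so that inference is not drawn here. The blinding statement covers only the interim survival analysis, so the toxicity case-note review does not contradict it.

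**Conclusion.** The concern holds in a limited form. That coded labels cannot conceal the SABR arm at 50 patients is certain: it follows from the stated allocation, strata and block size, and needs only a display that shows arm sizes.

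The effect on the final test is conditional. Two-sided alpha stays near 0.20 if re-sizing follows pooled data alone. If the by-arm result influences the choice, the worst case is about 0.22 to 0.26 under moderate assumed limits at 26 interim deaths, and about 0.35 with almost none. These are upper bounds on a possibility that the text leaves open, not estimates of what will happen. They assume exponential survival, two-sided alpha and an unadjusted final test.

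The supportable conclusion is that the trial could not demonstrate that its final size was chosen independently of the interim comparison. This is a moderate point that is best settled before the 50-patient look.

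**What to change.** 1. Delete the claim of blinding, or state that the committee is effectively unmasked at this look while the sponsor and investigators stay blind to comparative survival.
2. Have any change in accrual made from pooled data only, by an existing trial statistician with no access to by-arm results.
3. State the benchmark: either a pooled median, with the hypothesis it belongs to (about 12.6 months under the alternative, 9 under the null), or the roughly 78 deaths implied by the design. Say how large a departure triggers a change, and set lower and upper limits on N.
4. If by-arm results are meant to inform the size, say so and use a combination or conditional-error test at the end.

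The cost is protocol and charter wording, with no extra patients. The downside is that the committee gives up its discretion over re-sizing.

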## Discussion

Although the aggressive treatment of patients with oligometastatic disease has become more common over the last decade [24], considerable equipoise still exists as to whether such aggressive treatments improve overall survival, or whether the long-term survival seen in single-arm studies is due to patient selection and treatment of slow-growing, favorable tumors [25]. Although SABR and surgical resection of oligometastases are generally safe, there is a risk of toxicity, and a small risk of treatment-related mortality [26,27]. Since patients with metastatic disease have traditionally been considered to be best served by palliative treatments, it is incumbent upon physicians to demonstrate that the escalation of treatment (with attendant risks of side effects or complications) is associated with gains in survival and/or quality of life.

This multicenter, international study aims to accrue 99 patients and aims to provide preliminary evidence to assess the impact of a comprehensive oligometastatic SABR treatment program on overall survival and quality of life. Data from this study may be used to inform the design of a phase III study, and will lead to a better understanding of the oligometastatic paradigm.

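### The single interim survival rule sets the same p < 0.001 bar for harm as for benefit; a non-binding harm guideline at that look would be a cheap improvement

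*Protocol article*

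**What the plan says.** The section on the data safety monitoring committee (DSMC) in the Protocol article sets one look at survival: "The DSMC will conduct one interim analysis once 50 patients are accrued". At that look "the DSMC will be blinded to the identity of each treatment arm, but OS data will be presented for each arm". The stopping rule is "The DSMC will recommend stopping the trial if there is an OS difference that is statistically significant with a threshold of p < 0.001", by log-rank test. The text names neither a direction nor a sidedness, and because the arms are masked the rule has to be applied identically whichever arm is doing worse.

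Two other provisions stand in the same section:

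- A toxicity clause begins "If the DSMC deems that toxicity rates are excessive (>25% grade 3 toxicity, or >5% grade 4 or 5 toxicity") and leaves any recommendation to the committee's discretion, after case-note review of whether grade 3–5 events are related to treatment. The annual meetings are for toxicity.
- A clause on median survival in all patients combined allows the accrual target to be changed. It does not compare the arms.

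Under Sample size the protocol states "The study will therefore be designed with alpha = 0.20 and beta = 0.20" and "It is estimated that the median survival of the control group after randomization in this study will be 9 months", with accrual of "20 patients in year 1, and 25-30 patients in years 2, 3, and 4". The Discussion acknowledges that with SABR and surgical resection "there is a risk of toxicity, and a small risk of treatment-related mortality".

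**The concern.** A very strict interim limit is normally justified by the need to protect the final type I error against an early claim of benefit. That reason does not carry over to harm, because stopping for harm cannot produce a false claim of benefit. Used in both directions, the limit asks for near-certainty that an intensified treatment shortens survival before the written rule responds, in a trial whose final test accepts alpha = 0.20.

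After the look, 99 − 50 = 49 patients remain to be randomised, about two-thirds of them (33) to SABR. If SABR led to more deaths that nobody attributed to it, for example deaths recorded as progression, the survival rule is the only written criterion that would count them.

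**Working it through.** **Inputs from the protocol.** Control median 9 months; target median 15 months (hazard ratio 9/15 = 0.60 if exponential); allocation 1:2 in blocks of nine; accrual of 20 in year 1, then 25–30 a year; 48 months of accrual plus 12 of follow-up; 93 patients before loss, 99 after.

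**Assumptions not in the protocol.** Exponential survival, proportional hazards, no loss before the look, data cut at entry of the 50th patient, unstratified log-rank test, p < 0.001 read as two-sided (|z| > 3.29).

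**Step 1: reproduce the plan's sample size.** Deaths = (1.282 + 0.842)² / [(1/3)(2/3)(ln 0.60)²] = 4.51 / (0.2222 × 0.2609) ≈ 78 for two-sided alpha 0.20. With an overall death probability of 0.811, N = 78/0.811 ≈ 96. The Lachin–Foulkes formula gives 94.5 and a log-hazard variance formula 91.6; power at N = 93 is 0.791. The stated 93 is therefore reproduced as a two-sided design. One-sided alpha 0.20 would need only about 60.

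**Step 2: timing of the look.** After 20 patients in year 1, the next 30 take 12 × 30/30 = 12 to 12 × 30/25 = 14.4 months, so the 50th patient enters at about month 24 to 26.

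**Step 3: what the rule demands.** The observed hazard ratio at the boundary is about exp[3.29 / √(D × 2/9)] for D deaths. With D = 30 this is exp(3.29/2.58) ≈ 3.6; with D = 34, exp(3.29/2.75) ≈ 3.3.

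**Step 4: how often it is crossed.** Log-rank simulation, 10,000 trials per scenario. Ranges cover the stated yearly accrual and uniform accrual of 99 over 48 months.

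| True HR (SABR vs control) | Deaths at look | Crosses p < 0.001 for harm | One-sided 0.05 | One-sided 0.025 |
|---|---|---|---|---|
| 1.0 | 26–27 | 0.02–0.03% | about 4.6% | 2.2–2.4% |
| 1.5 | 30–31 | 0.6–0.9% | 24–26% | 15–16% |
| 2.0 | 32–33 | 4.1–4.6% | 53–55% | 40–42% |
| 2.5 | 34–35 | 13–15% | 75–77% | 63–65% |

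**Step 5: sensitivity at HR 2.0.** Changing one assumption at a time, the chance of crossing the existing rule is:

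- 6.4% to 1.0% for control medians of 6 to 24 months;
- 8.4% or 9.6% with the data cut 6 or 12 months later;
- 6.5–7.2% if p < 0.001 is read as one-sided;
- 7.6–8.0% by the Schoenfeld approximation instead of simulation;
- 16% by Schoenfeld even if all 50 patients had died.

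**Step 6: cost of a harm limit.** At the planned HR of 0.60, one-sided 0.05 towards harm is crossed in only about 0.2% of trials. Simulated power for the full 99-patient trial with readout at month 60 is 82.32% without and 82.29% with that limit, even if every crossing stopped the trial.

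**The case against.** - **A symmetric strict limit is a common convention, and nothing in the section is misstated.** That stands. How much evidence of harm to require is a judgement, so this is an improvement to a design choice and not the correction of an error.
- **Crossing one rule is not the same as stopping the trial.** A reader might infer from the table that the trial would almost always run on if SABR doubled the death rate. The protocol does not support this: p < 0.001 is a condition that triggers a recommendation, and nothing forbids the committee from acting on less. It sees survival by arm at the look and reviews toxicity every year.
- **Treatment-related deaths are already covered.** A reader might also infer that the acknowledged risk of treatment-related mortality goes unguarded. It does not: such deaths are grade 5 toxicity and fall under the 5% limit for grade 4–5. Taking about 33 SABR patients as the denominator, two events give 2/33 = 6.1%, already above the limit. If the true rate were 10%, the chance of at least two is 1 − 0.9³³ − 33 × 0.1 × 0.9³² ≈ 86%. What survives is that this route is discretionary and depends on attribution.
- **The chemotherapy-free window is not a SABR-only hazard.** The Chemotherapy section applies it to conventional radiotherapy as well as SABR, so it should not be used as the example of an uncounted SABR risk.
- **A hazard ratio of 2.0 is extreme.** It implies a 4.5-month SABR median in patients required to have a life expectancy above 6 months. The protocol gives no reason to expect it; it shows the rule's sensitivity and is not a forecast. At the milder 1.5 the rule is less sensitive still.

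**Conclusion.** The point holds as a cheap improvement. The one written rule that compares deaths between the arms has a chance of only about 1%, 4–5% and 14% of responding to true hazard ratios of 1.5, 2.0 and 2.5 at the planned look. At 2.0 it stays below 10% when the control median, the data cut or the sidedness is varied singly in simulation. The gap is confined to excess deaths not attributed to SABR; attributed deaths have their own limit, and the committee keeps its discretion. The figures rest on exponential survival, proportional hazards and a data cut at the 50th entry.

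**What to change.** Keep p < 0.001 for stopping on benefit. At the same single look, add a non-binding guideline: the DSMC considers recommending a pause or stop if overall survival favours Arm 1 at one-sided p < 0.05 (or 0.025), and the reporting statistician tells the committee which arm the difference favours.

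**Gain.** At a true hazard ratio of 2.0, about 54% (or 41%) of trials would be flagged, against 4–5% now.

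**Cost.** One or two sentences in the protocol and any DSMC charter; about a 5% (or 2%) chance of a false flag when there is no effect; and loss of the committee's arm masking, which groups of about 17 and 33 largely give away already. Power at the planned effect stays at about 82.3%, and the false-positive rate for benefit does not rise.

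Do not extend the harm comparison to later annual meetings unless the operating characteristics of the multi-look rule are computed first. The gains above belong to one look only: a one-sided 0.05 limit at each of three looks (months 25, 36 and 48) would raise the false flag to about 9%, while splitting 0.05 equally over three looks would cut first-look detection at a hazard ratio of 2.0 to about 34%.
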